### Study endpoints

The primary endpoint of this study is 30-day all-cause mortality. Secondary outcomes include the following:(1) 60-day all-cause mortality;(2) The proportion of clinical deterioration, which is defined as the need within 30 days after administration for admission to the intensive care unit or invasive mechanical ventilation/ extracorporeal membrane oxygenation (ECMO), or all-cause mortality;(3) Mean change in clinical status using the 8-point-ordinal-scale from day 1 (baseline) to day 15 and day 22 (optional);(4) Time to sustain clinical recovery (determined using an 8-point ordinal scale);(5) Percentage of subjects reaching sustained clinical recovery (determined using an 8-point ordinal scale) on days 5, 8, 15, and 22 (optional);(6) Mean change in the Acute Physiology and Chronic Health Evaluation II (APACHE-II) scores from day 1 (baseline) to days 15 and 22 (optional);(7) Changes in oxygenation index measured by blood gas analysis or blood oxygen saturation from day 1 (baseline) to days 3, 5, 8, 15, and 30 (optional);(8) Changes in chest CT scan (optional) from baseline to day 8 or 15;(9) Percentage of subjects confirmed negative for SARS-CoV-2 RT-PCR by nasopharyngeal (NP) swab on days 3, 5, 8, 15, and 30 (optional);(10) Change in Ct values of SARS-CoV-2 RT-PCR on days 3, 5, 8, 15, and 30 (optional);(11) Safety assessments (eg, AEs, serious AEs, and abnormal laboratory data) from the time of SARS-CoV-2 RT-PCR turned negative to day 30.

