The 8-point ordinal scale is an assessment of the clinical status at the first assessment of a given study day. The scale is defined as follows: (1) Death; (2) Hospitalized, on invasive mechanical ventilation or ECMO; (3) Hospitalized, on non-invasive ventilation or high flow oxygen devices; (4) Hospitalized, requiring supplemental oxygen; (5) Hospitalized, not requiring supplemental oxygen- requiring ongoing medical care (COVID-19 related or otherwise); (6) Hospitalized, not requiring supplemental oxygen, and no longer requires ongoing medical care; (7) Not hospitalized, limitation on activities; (8) Not hospitalized, no limitations on activities [21].

APACHE II score is a severity score and mortality estimation tool developed from a large sample of ICU patients, which consists of an acute physiology score (APS), the age of the patient, and chronic health points. And APACHE II score is made of 12 physiological variables and 2 disease-related variables. The maximum APACHE-II score is 71, though it is rare for a patient to score higher than 55. When APACHE II scores are combined with an accurate description of the disease, they can prognostically stratify acutely ill patients and assist investigators in comparing the success of new or differing forms of therapy [22, 23].

Nasopharyngeal swabs will be performed following a standardized procedure in this trial [24]. In addition, the result of NP SARS-CoV-2 RT-PCR will be adopted, if patients have already tested for NP SARS-CoV-2 RT-PCR no more than 48 h before the first drug administration. The viral clearance of COVID-19 in the treatment period defines as the results of both tests (the first test and retested 24 h later) being negative SARS-CoV-2 RT-PCR test or Ct values > 35.

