### Statistical analysis

All efficacy analysis results are analyzed in the full analysis set (FAS) and per-protocol set (PPS). The FAS is defined as all randomized patients who received at least one dose of the study drug. The PPS is defined as all patients who completed the treatment without serious violation of the protocol. The safety analysis will be performed based on the FAS and no imputation will be made for missing safety data. Categorical data will be expressed as numbers and percentages, and quantitative data will be expressed as means ± standard deviation (SD), median, interquartile range (IQR) values, or minimum and maximum. The primary outcome will be an analysis of the percentage of 30-day all-cause mortality. The analysis of efficacy in the secondary endpoint measures will be based on their variable attributes in an appropriate way. For binary variables, the exact probability method will be used to calculate the probability of the subject with clinical deterioration. For continuous variables, the value of actual measured values and the chances from the baseline will be summarized. For rank variables such as changes in the score of the 8-point order scale, the paired Signed Rank Test method will be used. For time-to-event variables, the Kaplan–Meier method will be used to estimate the median and Kaplan–Meier graphs will be provided. All statistical analyses will be performed using Statistical Analysis System 9.4 (SAS Institute, Inc, Gary, NC), and statistical significance was set at *p* < 0.05.

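### Kaplan–Meier for time to sustained recovery, with follow-up ending at death, treats patients who die as still able to recover; by default the plan overstates recovery and shortens the median

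*Protocol article*

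**What the plan says.** Under Study endpoints, the fourth secondary outcome is time to sustained clinical recovery, judged on the 8-point ordinal scale. Under Statistical analysis, all such variables get one method: "For time-to-event variables, the Kaplan–Meier method will be used to estimate the median". Follow-up and data collection ends observation at 60 days or at death, whichever is earlier.

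APACHE II (mean change to days 15 and 22) and oxygenation index (change to days 3, 5, 8, 15 and 30) are continuous secondary outcomes. For these the section says: "For continuous variables, the value of actual measured values and the chances from the baseline will be summarized".

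Neither sentence says how a patient who dies enters the analysis. The only statement on missing values is limited to safety: "no imputation will be made for missing safety data".

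Death is counted elsewhere. It is the primary endpoint at 30 days and a secondary endpoint at 60 days, a component of the clinical deterioration outcome, and category 1 of the ordinal scale.

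**The concern.** A patient who has died cannot recover. Kaplan–Meier assumes that a censored patient keeps the same chance of the event as those still under observation. If observation stops at death and the death is entered as censoring, the curve estimates recovery in a setting where nobody dies. That figure is always at least as high as the proportion of enrolled patients who recover, and the gap widens with mortality.

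This matters more here than in a randomised trial. With a single arm, no control group shares the bias, and the absolute median and recovery percentage are the reported result. The Discussion says the trial will supply strong evidence to guide treatment. The bias is also largest when the drug does not reduce mortality, which is when a favourable recovery curve would mislead most.

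The APACHE II and oxygenation summaries have a related problem. A dead patient has no later measurement, so unless a rule is added the mean change at each visit describes those alive and measured. Losing the sickest patients can make that mean look better.

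**Working it through.** **The plan's own figure.** The protocol gives no figure for recovery. Its one computed figure, 58 evaluable patients, reproduces: in an exact binomial test of 12% against 2% with 0.025 in the lower tail, 58 is the smallest n with at least 80% power (success at 2 or fewer deaths, tail error 0.0239, power 0.890). The present point does not touch it.

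**Inputs from the protocol.**
- Mortality expected on treatment: 2% (Sample size calculation).
- Mortality assumed under standard therapy: 12% (Sample size calculation).
- Upper end of the range cited for hospitalised patients: 14.1% (Sample size calculation).
- Mortality cited for critical cases only: 60.5% (Background).

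**Assumptions.** True 30-day recovery R of 50% to 80%; constant hazards of recovery and death over 30 days; D, the proportion dying before recovery, set equal to the mortality figure; no other censoring.

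**Formulas.**
- Total hazard: h = −ln(1 − R − D)/30.
- Recovery hazard: a = h × R/(R + D).
- Kaplan–Meier with deaths censored: recovered by day 30 = 1 − exp(−30a); median = ln 2/a.
- Competing-risk median: the t that solves [R/(R + D)] × [1 − exp(−ht)] = 0.5.

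**Worked case, D = 12%, R = 60%.**
- h = −ln(0.28)/30 = 0.04243 per day; a = 0.04243 × 0.60/0.72 = 0.03536 per day.
- Kaplan–Meier: 1 − exp(−1.061) = 65.4% recovered; median 0.6931/0.03536 = 19.6 days.
- Competing risk: 60% recovered by construction. The median solves 1 − exp(−ht) = 0.5 × 0.72/0.60 = 0.60, so t = −ln(0.40)/0.04243 = 21.6 days.
- Overstatement: 5.4 points; the median is 2.0 days too short.

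**Range.**

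| Mortality | True recovery | Kaplan–Meier | Overstatement (points) | Median, Kaplan–Meier vs competing risk (days) |
|---|---|---|---|---|
| 2% | 50% | 50.6% | 0.6 | 29.5 vs 30.0 |
| 2% | 60% | 60.8% | 0.8 | 22.2 vs 22.5 |
| 2% | 80% | 81.2% | 1.2 | 12.4 vs 12.6 |
| 12% | 50% | 54.2% | 4.2 | 26.6 vs 30.0 |
| 12% | 60% | 65.4% | 5.4 | 19.6 vs 21.6 |
| 12% | 80% | 88.9% | 8.9 | 9.5 vs 10.2 |
| 14.1% | 50% | 55.0% | 5.0 | 26.0 vs 30.0 |
| 14.1% | 80% | 91.0% | 11.0 | 8.6 vs 9.4 |

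**Extreme case.** At 60.5% mortality recovery cannot exceed 39.5%, so 35% is assumed. Kaplan–Meier then gives 67.9% (32.9 points too high) and a median of 18.3 days. Under the competing-risk model recovery levels off at 0.35/0.955 = 36.6%, so no median exists.

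**Deaths kept at risk.** If patients who die stay in the risk set as not recovered to the end of follow-up, Kaplan–Meier equals the cumulative incidence and the overstatement is 0.

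**Scale.** In 64 patients the expected deaths are 64 × 0.02 = 1.3 or 64 × 0.12 = 7.7.

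For APACHE II and oxygenation the documents give no expected values, so the size of the survivor effect cannot be calculated.

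**The case against.** The strongest reply is that the protocol never says deaths are censored. It names Kaplan–Meier, and one of the two remedies can be run within Kaplan–Meier. Censoring rules are commonly left to a statistical analysis plan, which is not shown. It stands that the fault is not written down as such, and no one should report that the plan orders censoring at death. But the estimator is fixed in the text and observation ends at death, so censoring is what happens unless a rule is added.

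A second reply is that size and stakes are modest. At 2% mortality the bias is about 1 point. At 12% mortality and 60% recovery it is 5.4 points, against a 95% half-width of 1.96 × √(0.6 × 0.4/64) = 12 points. These are secondary, descriptive outcomes of an exploratory trial, and deaths are reported separately. All of this stands and limits the weight of the point. Still, a bias in a known direction is not excused by a wide interval, and 2% is the effect hoped for.

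A third reply is that the sentence on continuous variables most naturally means raw values plus changes from baseline, not a decision to exclude the dead. That also stands. The shortcoming is an unlabelled population, not a stated exclusion.

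**Conclusion.** The point holds for time to sustained recovery. The named estimator, applied in the ordinary way with follow-up ending at death, overstates recovery and shortens the median. On the assumptions above (50% to 80% recovery, constant hazards), the overstatement is about 1 point at 2% mortality and about 4 to 9 points at 12%. It is larger if mortality approaches the figure cited for critical cases. For APACHE II and oxygenation the point is only that the mean change needs a label and a count of deaths.

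Four stronger readings might be inferred, and the documents support none of them:
- That the secondary analyses as a whole ignore death. The ordinal scale, the deterioration composite and 60-day mortality all count it.
- That the 33-point case is the expected one. The 60.5% is cited for critical cases only, whereas the trial enrols severe or critical patients, and the 35% recovery beside it is an assumption.
- That deaths should be given the top APACHE II score. The sentence "The maximum APACHE-II score is 71, though it is rare for a patient to score higher than 55" only describes the scale's range; imputing that value would replace the stated mean change with a different quantity.
- That the recovery and PCR-negative percentages drop the dead. Nothing removes them from the full analysis set.

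The primary endpoint and the sample size are unaffected.

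**What to change.** State that time to sustained recovery will be estimated by cumulative incidence (Aalen–Johansen) with death as the competing event, or equivalently that patients who die stay in the risk set as not recovered to day 60. Read the median from that curve, and report it as not reached if fewer than 50% recover.

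Keep the APACHE II and oxygenation mean changes, label them as describing patients alive and measured at each visit, and give the number of deaths to date beside each. A median with deaths given the worst rank may be added as a sensitivity analysis.

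The cost is a few sentences of analysis wording and standard procedures in the SAS version already named. No extra data or patients are needed. The downside is that the recovery figures will look slightly less favourable.

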### Safety analysis

Adverse events are coded using the medical dictionary for regulatory activities (MedDRA) [27]. In this trial, statistical analysis is mainly performed for treatment-emergent adverse events (TEAEs), and pretreatment adverse events will be listed in a list. The number and proportion of all adverse events, drug-related adverse events, serious adverse events, severe adverse events, and adverse events leading to discontinuation of the drug will be calculated. Adverse events will be classified and statistically analyzed at two levels: system organ class (SOC) and preferred term (PT).

### Confidentiality

All communications, reports, and subject samples will be identified by site number, code number, and initials to maintain subject confidentiality. All records will be kept confidential to the extent permitted by law. If a waiver or authorization separate from the statement in the informed consent is required for permitting access to the medical records of a subject, the investigator will obtain such authorization before enrolling the subject in the study. The investigator should keep a separate log of subjects, codes, names, and addresses. Documents that identify the subject by name (eg, the informed consent forms) will be kept in strict confidence.

The sponsor and its business associates agree to keep all subject information confidential. Data resulting from analyses will be entered into a database that is not accessible to the public. Subject data will be identified only by the subject screen number, randomization number, and initials, and not by any other annotation or identifying information. The sponsor and its business associates will take every possible step to reduce the risk of releasing information to the public that would enable subjects to be personally identified.

### Interim analyses

There are no planned interim analyses.

### Oversight and monitoring

In this trial, the investigator or whose representative will conduct regular monitoring visits to evaluate whether the study is implemented in compliance with the study protocol according to good clinical practice (GCP) and whether the data are appropriately corrected. To make sure validation of the data, the investigator and institutions will allow their representatives, as well as relevant regulatory authorities, direct access to the original documents for data validation. The trial center requires review by an independent research ethics committee or institutional review boards and a relevant regulatory agency.

### Dissemination plans

The principal investigators will be responsible for the publication of the data and are committed to publishing and disseminating it promptly without excessive restriction. Findings will be published in peer-reviewed journals and disseminated through various channels including social media and at national and international meetings. The proposed publication should not include any sponsor information or any personal data of any subject (eg, name or initials) except the study results.

## Discussion

COVID-19 is a new and poorly understood disease that posed a huge challenge to global public health. Most patients with COVID-19 have mild symptoms, but some patients rapidly develop severe and critical illnesses, and the mortality of critically ill patients with COVID-19 is high [28]. Previous reports revealed that androgen-mediated expression of ACE-2 and TMPRSS2 related to the degree of severity and mortality of COVID-19 disease [29–31]. Proxalutamide as a novel potent AR antagonist has been shown to downregulate the expression of ACE2 and TMPRSS2 in lung cancer cells, and also accelerate viral clearance in mild to moderate patients with COVID-19 [32]. But the efficacy of proxalutamide treatment for severe and critically ill COVID-19 patients is unclear. Therefore, a single-arm, open-label, prospective exploratory trial is designed to investigate the efficacy and safety of proxalutamide in the treatment of severe and critically ill patients with COVID-19 for the first time.

This trial has several strengths. First of all, this is the first prospective study of proxalutamide in the treatment of severe or critically ill patients with COVID-19 in China. Currently several clinical trials of proxalutamide in COVID-19 are focused primarily on mild to moderate patients, all patients without the severity of illness, or mechanism of action for proxalutaminde treatment [16, 33, 34]. Our study will provide sufficiently strong evidence to guide the treatment of severe or critically ill patients with COVID-19. Secondly, there are no specific therapeutic agents or vaccines for COVID-19 available. This trial study on androgen receptor antagonists which is a novel therapeutic target in COVID-19, inhibiting SARS-CoV-2 infection by regulating ACE2 and TMPRSS2. It may provide a basis and reference for other androgen receptor drugs with similar mechanisms in COVID-19. Moreover, this study allows patients to use convalescent plasma from recovered COVID-19 patients, SARS-CoV-2 monoclonal antibody therapy, and corticosteroid during the treatment period. Under these conditions can represent the real world of the treatment of COVID-19 as accurately as possible.

Despite the above strengths, there are still some limitations in the present study. Firstly, our sample size was small and the trial was conducted at one center. However, as the COVID-19 pandemic is a sudden and temporary event, the center for accepting and treating severe or critically ill patients with COVID-19 is limited and temporally, meanwhile, the number of recruited severe or critically ill patients at clinical centers may be low. Secondly, this trial did not include a control group, therefore, reducing the generalizability of our results. Because there is no approved effective conventional treatment for patients with severe or critical COVID-19. Given the ethical considerations of protecting the maximum benefits of participants and the objectives (rapid discovery of proxalutamide efficacy) of this investigator-initiated clinical trial, no control group was recruited for this study. Randomized controlled trials will continue to be conducted in the future to assess the effect of proxalutamide. Thirdly, this is an open-label trial, considering severe or critically ill patients with COVID-19 may deal with invasive treatment delivered in the ICU (including ECMO), which is undoubtedly more difficult or impossible to conduct a blinded trial. But blind will be maintained for all other members of the clinical and research team, such as statistical staff, to minimize bias.

In summary, the present trial is the first to investigate the efficacy and safety of proxalutamide in severe or critically ill patients with COVID-19. The findings of this study might provide convincing evidence regarding the efficacy and safety of proxalutamide on severe or critically ill patients with COVID-19.

### Trial status

Participant recruitment started on 16 May 2022, with 64 participants recruited by 16 May 2023.

## Data Availability

The datasets during the current study are available from the corresponding author on reasonable request after the main results have been published, as long as it corresponds with the local rules and regulations for data sharing.

## Abbreviations

AR: Androgen receptor
ACE2: Angiotensin-converting enzyme 2
AEs: Adverse events
COVID-19: The 2019 coronavirus
DMP: Data Management Plan
EGG: Electrocardiography
ECMO: Extracorporeal membrane oxygenation
eGFR: Estimated glomerular filtration rate
ICU: Intensive care unit
IIT: Investigator-initiated trial
PPS: Per-protocol set
PT: Preferred Term
TMPRSS2: Transmembrane protease serine 2
TEAE: Treatment-emergent adverse event
TESAE: Treatment-emergent serious adverse event
ULN: The upper limit of normal
SOC: System organ class
